## Abstract

(1) *Background*: Sleep disorders are a common problem for public health since they are considered potential triggers and predictors of some mental and physical diseases. Evaluating the sleep quality of a person may be a first step to prevent further health issues that diminish their independence and quality of life. Polysomnography (PSG) is the “gold standard” for sleep studies, but this technique presents some drawbacks. Thus, this study intends to assess the capability of the new Xiaomi Mi Smart Band 5 to be used as a tool for sleep self-assessment. (2) *Methods*: This study will be an observational and prospective study set at the sleep unit of a hospital in A Coruña, Spain. Forty-three participants who meet the inclusion criteria will be asked to participate. Specific statistical methods will be used to analyze the data collected using the Xiaomi Mi Smart Band 5 and PSG. (3) *Discussion*: This study offers a promising approach to assess whether the Xiaomi Mi Smart Band 5 correctly records our sleep. Even though these devices are not expected to replace PSG, they may be used as an initial evaluation tool for users to manage their own sleep quality and, if necessary, consult a health professional. Further, the device may help users make simple changes to their habits to improve other health issues as well. Trial registration: NCT04568408 (Registered 23 September 2020).

## 1. Introduction

Sleep is an occupational area that has considerable implications on our daily life [1,2]. Thus, sleep disorders have become one of the most important common problems in public health [3]. The prevalence of sleep disorders increases with age [4], even though they can appear at any life stage. Bad quality and quantity of sleep, sleep arousals, and a strong will to take diurnal naps are the main complaints among the general population [5,6]. Epidemiological studies indicate that between 20% and 48% of adults between 34 and 60 years old have difficulties initiating and maintaining sleep [7]. In fact, insomnia, which is the most common sleep disorder, is present in 30–45% of the population [8].

Several studies state that sleep disorders are related to health status and quality of life in the general population [9], leading to difficulties in the performance of daily life activities, which in turn causes physical exhaustion, low productivity, a greater risk of falling, mood problems, and diurnal sleep, among many others [10,11,12,13,14].

These factors related to sleep disorders cause a direct and indirect economic burden, causing public health costs to rise [15,16]. Different studies have shown a direct relation between sleep disorders and costs in primary care and hospitals. Lee et al. indicated that the population suffering from sleep disorders regularly attends the emergency room to consult professional health workers, or demands telematic assistance [9]. This is due to subjective complaints of sleep, along with factors related to stress, working pressure, and other chronic diseases [17,18].

Diverse sleep disorders are diagnosed using different tests that assess the quality and quantity of sleep [19,20]. Objective and valid diagnostic tests that evaluate the quality and quantity of sleep are a previous requisite for the control of sleep disorders [21]. Polysomnography (PSG) is considered by the scientific community as the most reliable test for the measurement of sleep parameters [22,23]. However, it has some clear drawbacks, such as its costs, operation, invasiveness, and time needed for its use [24,25]. To address these problems, actigraphy technology was designed. Actigraphy consists of the measure of sleep parameters using a wearable device created for clinical use [26]. Several studies have found similar measures from both actigraphy and PSG, proving its fitness for these studies [27,28,29]. Although actigraphy has become a clinically useful tool to test sleep disorders, it cannot provide feedback to people because it purpose is mainly of a research nature [26]. Thus, inspired by the actigraphy device, researchers have recently focused on the validation of different tools for sleep self-assessment, such as activity wristbands [30].

In recent years, activity wristbands have become widely accepted among the population due to their low price, easy use, smart design, and feedback that they offer to users through their fast sync with smartphones, boosting participatory health [31,32,33]. These devices have already reported benefits in clinics, as they reduce care burdens and facilitate the early diagnosis of health disorders [34]. They also allow the general population to acquire information on their sleep quality and physical activity, which may help in the early detection or prevention of symptoms related to sleep alterations [35,36,37].

Despite being limited, some studies highlight the importance of the validation of these devices not only from a technological point of view, but also for health promotion, since, by allowing sleep self-assessment, they are tightly related to improvements in life quality and daily functioning [38,39,40,41].

Recent studies have compared the measurements of these wristbands with those of actigraphy and PSG techniques. PSG involves different types of electrodes (electroencephalogram (EEG), electrooculogram (EOG), electromyogram (EMG), and electrocardiogram (ECG)) to classify the stages of sleep [42]. A few studies have shown that the usability of an ECG signal can determine the stages of sleep [43,44,45,46]. Nevertheless, some have considered the need for further research due to the insufficient quality of this classification compared to the combination of the other electrodes [47,48].

In general, wearable devices can determine the stages of sleep through a heart rate (HR) sensor, which measures the HR, and an accelerometer that detects movement. Previously validated wearable devices have shown a high precision and sensitivity, but also a low specificity and poor agreement in sleep-stage classification when compared with PSG [20,32,33,49,50]. It would be logical to expect these devices to measure sleep more accurately; however, according to these studies, there is a wide range of improvements that can still be accomplished [51,52]. As a result, this protocol has been designed to validate the Xiaomi Mi Smart Band 5 due to its low cost and high acceptance among users, as it is the best-selling fitness tracker [53]. This device has the capability of tracking the activity and HR of users, and classifies the user’s state as being awake or in light sleep, deep sleep, or REM sleep [54].

Therefore, this research focuses on determining whether sleep stages recorded by the new Xiaomi Mi Band 5 can effectively replace PSG sleep-stage classification in sleep-study participants. To this end, the following features will be calculated for both devices: total sleep time, sleep efficiency, sleep latency, and wake after sleep onset. Sleep stages will also be recorded.

Thus, the primary purpose of the present study is to validate the quality of the data generated by Xiaomi wearables when compared with the PSG technique from a hospital sleep unit.

The secondary objectives are: (1) to determine the total sleep time, sleep efficiency, sleep latency, and wake after sleep onset from both the wearable device and PSG; and (2) to examine whether the classification of sleep stages provided by wearable devices is comparable with classifications based on PSG.

## 2. Materials and Methods 

### 2.1. Study Design

This is a pilot study that aims “to demonstrate that the expected measures, data collecting instruments, and their management system are viable and effective” [55]. This is an observational and prospective study, which means that different variables from the population of interest will be observed and recorded without any direct intervention, in order to establish causality associations between these variables. It will be considered a longitudinal study, with a timeframe of six months, in which participants will stay one night at the sleep unit. They will be monitored to record their sleep through PSG and the Xiaomi wristband.

This study protocol follows the SPIRIT 2013 checklist for study protocols for clinical trials (See File S1) [56].

### 2.2. Study Settings

The setting of this study will be the sleep unit of a hospital in A Coruña, Spain. This service includes a special consulting room where different sleep disorders are diagnosed and treated. Some of these disorders are sleep apnea, insomnia, restless-legs syndrome, narcolepsy, the delay and advance of sleep stages, sleep terrors, somnambulism, and bruxism. The sleep laboratory is equipped to perform different diagnostic tests: nocturnal and diurnal PSG, multiple latency tests, immobilization tests, and wakefulness maintenance tests.

### 2.3. Eligibility Criteria

Sample selection will be performed through an intentional sampling based on inclusion and exclusion criteria.

Participant inclusion criteria: (a) having attended the sleep unit to have any diagnostic test done; (b) having declared an age that is equal to or higher than 18 years old.

Participant exclusion criteria: (a) having a significant health complication that hinders active participation in the study; (b) suffering from skin hypersensitivity or an allergic reaction due to the materials of the wristbands that will be used in the study.

### 2.4. Recruitment Process

This project will be conducted in the sleep unit of a hospital that, regardless of this study, people attend to have PSG tests done with the aim of detecting possible alterations in their sleep. The participants will be assisted by, at a minimum, the clinical neurophysiologist responsible for the sleep unit and a member of the research team. In the first meeting with each of the users, the clinical neurophysiologist responsible for recruiting the participants and monitoring them will inform them, if they meet the selection criteria, about the possibility of participating in the study and the implications of their participation, i.e., the use of an activity bracelet during the day or night and what is involved in the PSG test that will be performed on them. In addition, the mechanisms that will be followed to guarantee their anonymity and the confidentiality of their data will be clearly stated to the participants.

After the main characteristics of the research have been explained, each potential participant will be given an information sheet so that they can consult the information and make a decision before the test is carried out. Once the users return to the unit for testing, any doubts or queries will be resolved by the clinical neurophysiologist, and the informed consent document will be signed, if applicable, by the responsible professional and the person who expresses their final interest in participating in the study. In addition, if the participant has reading and writing difficulties, a witness must be present during the entire procedure to confirm that all the ethical processes have been respected by the research team. On the day of the PSG test, participants will arrive three hours before the test to become acquainted with the room, and will turn the lights on and off based on their sleep pattern. The specialized technical staff will control the test and will attend to any possible patient demands. Figure 1 shows the recruitment and the assessment process.

### 2.5. Justification of Sample Size

Differences equal or greater than 15 min in deep-sleep time between the measures of both methods are considered clinically relevant. Accepting a 0.05 alpha risk and a 0.1 beta risk (90% power) in a bilateral contrast, 43 subjects are needed to detect a difference that is equal to or greater than 15 min. Conservatively, a standard deviation of 30 for mean differences is assumed, according to previous studies [21,50,57].

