### 2.8. Data Analysis

The analysis will be performed by using the statistical software R. Numeric variables will be expressed as mean (M) and standard deviation (SD), including the range, minima, and maxima. Beyond simple data and study variable descriptions, inferential analysis will be performed in order to determine possible significant relationships between the variables of the study.

A paired-sample Student’s t-test will be used to compare the means of the different sleep parameters of interest. T-test effect sizes are 0.2 (small effect), 0.5 (moderate effect), and 0.8 (large effect), so if the means of two groups do not differ by a 0.2 standard deviation, the difference is trivial, even if there is a statistically significant relationship. [62]. Bland–Altman plots will be used to assess the concordance between both devices for each of the sleep parameters (total sleep time, sleep efficiency, and wake after sleep onset). A positive bias indicates that the device tends to underestimate a variable when compared with PSG. A negative bias indicates that a sleep variable is overestimated [63]. Point estimations will be calculated, as well as their 95% confidence interval.

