## 3. Discussion

The validation conducted in this study will allow us to evaluate whether the Xiaomi Mi Smart Band 5 is a device that can be used as a health promoter by allowing sleep self-assessment in the general population. Due to its low price, it is fairly accessible to any user who considers that they may be suffering from a sleep disorder that is potentially worsening their health [32]. Hence, if the data generated by the smart band proves to be reliable, any health professional could evaluate at a glance whether the user is suffering from a sleep disorder, and whether it influences their daily life activities [40,67]. The widespread use of these devices could help users to self-assess their sleep and connect with health professionals in the case of bad sleep quality, which would imply a better prognosis and a longer and higher-quality life expectancy. It is important to highlight some limitations and risks in studies focused on the validation of wearables, since firmware updates may modify the sleep-tracking algorithm, and the intra-wearables’ sleep measurements do not perfectly match, even when multiple smart bands worn by the same user are identical.

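### The 15-min deep-sleep limit is applied only to a mean difference, and deep sleep is missing from the Bland–Altman list, so a person's error in deep-sleep minutes is not assessed although the claimed use is individual self-assessment

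*Protocol article*

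**What the plan says.** Section 2.5 sets the only clinical limit in the article: "Differences equal or greater than 15 min in deep-sleep time between the measures of both methods are considered clinically relevant". The limit then serves as the effect size of a test on the mean. The error rates of that test are set out as "Accepting a 0.05 alpha risk and a 0.1 beta risk (90% power) in a bilateral contrast", and the resulting size is that "43 subjects are needed to detect a difference that is equal to or greater than 15 min". The variability is given without a unit: "Conservatively, a standard deviation of 30 for mean differences is assumed, according to previous studies".

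Section 2.8 continues at the level of means: "A paired-sample Student’s t-test will be used to compare the means of the different sleep parameters of interest". It adds a triviality rule, also on means: "if the means of two groups do not differ by a 0.2 standard deviation, the difference is trivial". For agreement it says "Bland–Altman plots will be used to assess the concordance between both devices for each of the sleep parameters (total sleep time, sleep efficiency, and", with wake after sleep onset as the last item in the bracket. Deep sleep is not in that list. The text explains the sign of the bias and promises point estimates with 95% confidence intervals, but names no acceptable width for the differences.

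The same section plans an epoch-by-epoch analysis. Deep-sleep agreement there is the proportion of PSG deep-sleep epochs that the band also labels as deep.

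The claimed use is individual. The Discussion (section 3) asks whether the band is "a device that can be used as a health promoter by allowing sleep self-assessment in the general population" and foresees a health professional judging a single user from the band's data. The Abstract and the Conclusions (section 4) likewise speak of people managing or judging their own sleep.

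**The concern.** Over-readings and under-readings cancel in a mean. A person who reads the band does not benefit from that cancellation; what matters to that person is how far the one reading lies from the truth. Deep-sleep minutes carry the clinical limit and size the study, yet they are the quantity for which the text lists no analysis of individual differences.

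At stake is the step from results to conclusion. A small mean difference in deep sleep supports a statement about group averages. If it is read as support for self-assessment, the study says something about individuals that it has not measured.

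**Working it through.** **Inputs.** Limit 15 min, two-sided alpha 0.05, power 90%, SD 30, n = 43, all from section 2.5. Two assumptions are added: the SD is in minutes, and the paired differences are roughly normal.

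**1. The plan's own figure.** For a paired comparison, n = ((z₀.₉₇₅ + z₀.₉₀) × SD / δ)² = (3.2415 × 30/15)² = 42.03, rounded up to 43. The stated size is reproduced. This confirms that the 30 is the between-person SD of the band-minus-PSG differences and that the 15 min is applied to their mean. The sample-size arithmetic is not in dispute.

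**2. What the same inputs imply for one person.** With zero mean bias, P(|D| ≥ 15) = 2 × (1 − Φ(15/SD)), and the 95% limits of agreement are ±1.96 × SD.

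| SD (min) | Share off by 15 min or more | Limits of agreement (min) |
|---|---|---|
| 30 | 2 × (1 − Φ(0.50)) = 61.7% | ±58.8 |
| 25 | 2 × (1 − Φ(0.60)) = 54.9% | ±49.0 |
| 20 | 2 × (1 − Φ(0.75)) = 45.3% | ±39.2 |
| 15 | 2 × (1 − Φ(1.00)) = 31.7% | ±29.4 |

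The share passes one half at SD = 15/0.6745 = 22.2 min. The limits of agreement fit within ±15 min only if bias is zero and SD is at most 15/1.96 = 7.65 min.

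**3. How little the mean says about this.** With bias b, the share is 1 − Φ((15 − b)/SD) + Φ((−15 − b)/SD). At SD 30 it is 61.7% for b = 0, 62.4% for b = 6 (the 0.2 SD triviality bound, 0.2 × 30) and 65.9% for b = 15. Moving the mean across the whole clinical limit changes the individual error rate by about 4 percentage points.

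**4. Would an equivalence reading of the mean help?** At n = 43 and SD 30 the t-test is non-significant when the observed mean difference is below 2.018 × 30/√43 = 9.2 min. A band with zero bias and SD 30 is therefore non-significant in 95% of studies. In 100,000 simulated studies of that band, the 95% confidence interval of the mean lay wholly within ±15 min in 78.7%. A stricter test of the mean would not answer the individual question.

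**5. Does the epoch-by-epoch analysis fill the gap?** Its deep-sleep measure has PSG deep-sleep epochs as denominator. A band that detects all of them and also labels a stretch of light sleep as deep scores 100% on that measure, while its deep-sleep minutes are too high. The light-sleep proportion would fall and signal a problem, but in shares of epochs, not in minutes for a person.

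**6. What 43 pairs could deliver.** The standard error of a limit of agreement is SD × √(1/n + 1.96²/(2(n − 1))) = 30 × √(1/43 + 1.96²/84) = 7.88 min, so its 95% confidence interval is about ±15.9 min. If 16 of 43 participants were within 15 min (37%), the exact 95% interval would be 23% to 53%. Both are imprecise but informative.

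**The case against.** The plan does look at individual disagreement. A Bland–Altman plot shows every participant's difference, and limits of agreement are its usual output; the epoch-by-epoch measures do not cancel as a mean does; and sleep-stage identification stands first among the outcomes in section 2.6. This stands, and it would be wrong to read the t-test as the whole validation. It does not cover deep-sleep minutes, because the bracketed list defines the Bland–Altman parameters and leaves them out.

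The protocol calls its SD conservative, so 62% describes a cautious planning value and not the expected performance. This also stands, which is why the range is given.

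Acceptance limits for agreement are often left to an analysis plan. That is so, and the absence of a pass mark is not the point here. The article itself attaches a clinical limit to the mean and lists agreement parameters without the variable that carries it.

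Finally, section 2.5 uses 15 min only for the study-level contrast, and the sources behind it are not shown; a limit for one person's single night might differ. That is a fair caution, and a reason to report the limits of agreement in full alongside any count within 15 min.

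**Conclusion.** The point holds in a limited form. As written, the plan does not assess how far an individual's band deep-sleep time lies from PSG, and nothing ties the self-assessment conclusion to such agreement. At zero bias the share of users off by 15 min or more runs from 32% (SD 15) through 45% (SD 20) to 62% (SD 30), assuming minutes and roughly normal differences.

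A reader might infer that the plan would declare the band valid although it is wrong for most users. The documents do not support that. No rule makes the band valid from a non-significant test or a small mean difference, the study is described as a pilot, and the Discussion makes its claim conditional on the data proving reliable. A majority off by 15 min or more also requires, at zero bias, an SD above about 22 min. The gap is worth closing because it is cheap to close, not because the design fails.

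**What to change.** In section 2.8:

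- Add deep sleep to the Bland–Altman parameters, and report its 95% limits of agreement with confidence intervals, set against the 15-min limit.
- As a supplement, report the proportion of participants whose band deep-sleep time is within 15 min of PSG, with an exact 95% confidence interval. This dichotomises a continuous difference and has no pass mark, so it should not carry the conclusion alone.
- State that the t-test on means supports statements about group averages only, and that conclusions on individual self-assessment of deep sleep draw on these agreement measures together with the epoch-by-epoch results.

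The cost is a little more analysis on data already to be collected, with no extra participants. The downside is that the result may look less favourable to the band.

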### 2.6. Outcomes

The outcomes will be the sleep-stage identification of PSG and the Xiaomi Mi Smart Band 5, and measurements of total sleep time, sleep efficiency, sleep latency, and wake after sleep onset.

### 2.7. Data Collection and Management

The study will focus on examining the following variables (Table 1): time in bed, hours of light, deep and Rapid-Eye-Movement (REM) sleep, sleep efficiency, sleep latency, wake after sleep onset, and HR. Additionally, the Pittsburgh Sleep Quality Index (PSQI) scale and a sociodemographic questionnaire will be used to assess participants’ self-awareness of their sleep.

The sociodemographic questionnaire will collect different data: gender, year of birth, weight, height, handedness, sleep pathologies, and the assessment test. These data will be pseudonymized and transferred by the hospital to the research group with the prior consent of the participant.

The PSQI will evaluate subjective sleep quality. This questionnaire consists of 24 items about the area of sleep. This tool analyzes the quantity, quality, duration, latency, and efficiency of sleep [58].

The objective sleep data will be obtained through two different devices:

Xiaomi Mi Smart Band 5: This is a wearable device focused on health and sport that measures biomedical parameters of users, among which HR and sleep measurements are the most remarkable. The wristband also requires certain personal data from the user to precisely calculate the activity, such as age, height, weight, gender, handedness, and wristband location. Wristband data will be obtained from the Mi Fit application, which is the native app of the Xiaomi Mi Band wristband. It is necessary to connect the wristband via Bluetooth to a smartphone of general use for the group, creating generic emails for each of the wristbands. The features of interest will be calculated from the data shown in this app [32].

PSG: Data obtained from diurnal and nocturnal PSG will be collected, as this is the standard test for patients who attend to the hospital’s sleep unit. PSG measures sleep cycles and stages (N1, N2, N3, and REM sleep) by recording different variables, such as brain waves, eye movement, skeletal muscle activity, heart frequency and rhythm, blood pressure, oxygen level in the blood, breathing patterns, body position, limb movements, and whether there is snoring or other noise [59]. PSG parameters will be scored in 30 s epochs according to the American Academy of Sleep Medicine (AASM) guidelines [60], and PSG recordings will be exported in the European Data Format+ format [61] and interpreted by a doctor specialized in the study of sleep. Thus, sleep-stage classification based on PSG will be considered the “gold standard” for this study.

The data will be pseudonymized at the moment they are recorded; thus, the confidentiality of the data collected and the anonymity of each participant will be maintained. Once the project has ended, each participant’s data will be stored for future studies if they provide consent.

